## 6. Standardization

Three examiners will be standardized. Intra-and inter-examiner reliability of 90% will be achieved for plaque, bleeding, coronal caries and root remains measurements and 70% for periodontal measurements. Examiners will also be trained to take the subgingival dental plaque and saliva samples for oral microbiome analysis.

## 7. Infection Control Practices for COVID-19

Due to the characteristics of dental settings, the risk of cross infection may be higher between dental practitioners and participants. Interpersonal transmission of Severe Acute Respiratory Syndrome Coronavirus 2 (SARS-CoV-2) the pathogen of coronavirus disease 2019 (COVID-19) occurs mainly via respiratory droplets and aerosols, as well as contact transmission (86), symptomatic patients and patients in their incubation period are also carriers of SARS-CoV-2, and it remains to be fully established whether patients in the recovering phase are a potential source of transmission (87).

The standard protective measures in daily dental clinical work are not effective enough to prevent the spread of COVID-19 (87). Good hand hygiene and disinfection of all surfaces within the dental clinic will be implemented, 70% ethanol to clean and disinfect the blood pressure cuffs or thermometers will be applied, also surface sanitizers will be included 62–71% ethanol, 0.5% hydrogen peroxide, and 0.1% (1g/L) sodium hypochlorite. After each patient's visit, surfaces will be thoroughly wiped down (88). The reusable tools and materials will be cleaned, sterilized, and carefully preserved in compliance with the Protocol for the Disinfection and Sterilization of Dental Instrument (89). Whatever objects are removed from the patient's mouth (e.g., dental prosthesis) will be also disinfected (88).

Other standardized measures of maximum caution will be followed (90–92). The personal protective equipment for the examiners will include: N-95 masks, gloves, gowns, and goggles or face shields (87). Single-use devices will be applied (e.g., BP cuffs, etc.) to avoid cross-contamination. The number of appointments for evaluation will be reduced and no companions will be permitted in the dental clinic in order to avoid unnecessary aggregation. Any staff member who has COVID-19-related symptoms or has a close family member who is confirmed with the infection is advised to undergo a medical examination and cease working immediately (87). Pre-check triages to measure and record the temperature of every staff and participants will be done as a routine procedure. Pre-check staff will previously contact the participants to ask questions about the health status, symptoms such as cough and fever, history of contact and any visit to epidemic regions within the past 14 days. A positive answer to any of these questions will postpone the date of dental sampling for at least 4 weeks.

## 8. Data Coding and Recording

The information will be recorded in a data collection instrument designed *ad hoc* for this study. All the information will be registered in three relational databases: 1) the one that contains sociodemographic information, of factors associated with the development of systemic arterial hypertension and the registry of incidence of hypertension obtained from the umbrella cohort; 2) the oral health database which will contain the information from the interview and the dental clinical examination; 3) the database that will contain the information from the computational analysis of microbiomes.

## 9. Analysis

### 9.1. Statistical Analysis

A cross-sectional and longitudinal analysis of the information will be carried out as follows:

#### 9.1.1. Cross-Sectional Analysis

Descriptive statistics (proportion, mean, standard deviation, median, mode, and range, as appropriate) will be calculated to describe the oral characteristics of the participants during each 12-month period. Univariate analyses will be performed through parametric and non-parametric tests to explore the distribution of continuous variables based on defined exposure variables. In the same way, χ^2^ tests will be performed to explore the association of categorical variables with variables of interest. Multiple analyses (logistic regression, Poisson regression, negative binomial regression, generalized linear regression, gamma regression) will be performed to explore the association of the dependent variable with one or more independent variables while controlling for covariates.

#### 9.1.2. Longitudinal Analysis

As part of the longitudinal analysis the incidence of each oral variable included in the study in 30-month periods will be evaluated. Similarly the relative risk for each oral variable included will be evaluated according to different variables considered as risk factors (alcoholism, smoking, among others) through bivariate and multivariable analyses, using generalized linear models, logistic regression models, and multinomial regression models.

Starting with the third evaluation (baseline evaluation + first follow-up + second follow-up), trajectories of oral health conditions will be identified. From these variables associated with each one will be identified (gender, marital status, occupational class, age, education, among others). In the same way trajectories will be considered as risk factors for the development of hypertension in the study participants and will be included in neural network models.

For the statistical association analysis, participants will be classified in two groups: Group 1: without periodontitis and Group 2: with periodontitis (including all those participants that according to the CDC/AAP have mild, moderate, or severe periodontitis). For the sake of this association analysis and by following the consensus of the literature (73–75), participants in Group 2 who start periodontal treatment but do not continue with it until remission will be kept in this group and considered with periodontitis. However, a note will be made with details on the type, the extent of their treatment and the effects on their periodontal health, derived from their periodical periodontal evaluation.

This information will be used for a further *a posteriori* analysis. The information about the extent of their periodontal disease (mild, moderate and severe) will be also considered a posteriori. It is worth noticing that *a posteriori cluster analysis*, for instance, Propensity Score evaluation (93, 94) is not unusual in prospective observational studies subject to constraints, as is this case (95–99).

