### 3.3. Sample Size

#### 3.3.1. Sample Size for Periodontitis and Incidence of Hypertension

The projected sample size for periodontitis and incidence of hypertension will be 1212 individuals from those participating in the umbrella cohort. A logistic regression (LR) for a binary response (hypertension) on an independent variable (periodontitis) with a sample size of 866 participants (90% of whom are in group X = 0 and 10% are in group X = 1) achieves 90% power with 0.05 significance to detect a change in the Probability (Y = 1) of an estimated value of incidence of hypertension of 21.5%. This change corresponds to a Relative Risk (RR) of 2.4 (a RR between 1 and 2.74 has been reported) (6, 30, 36). An adjustment was made since the multiple regression of the variable of interest in the other independent variables in the LR obtained a *R*^2^ of 0.3. A 40% dropout rate is expected (*n* = 346), so the projected sample size will be 1,212 people.

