#### 3.6.2. Periodontitis

The periodontal evaluation will be done every year in terms of probing pocket depth (PPD) and clinical attachment loss (CAL). Examining 6-site-per-tooth in all natural teeth—except third molars–, measuring the distance from the cemento enamel junction (CEJ) to pocket depth and the distance from the gingival margin to the CEJ will be performed. Participants will be divided into two groups: (1) participants without periodontitis and (2) those with a diagnosis of periodontitis (mild, moderate and severe) based on *Centers for Disease Control and Prevention and American Academy of Periodontology* (CDC/AAP) definition (47), suggested for epidemiological studies by Holtfreter et al. (48). According to a recent agreement among experts from Europe and USA (48) and recent epidemiologic trends, the 2012 CDC/AAP criteria become a consensus approach for epidemiological studies worldwide (49). Furthermore, the 2017 World Workshop on the Classification of Periodontal and Peri-Implant Diseases and Conditions (50), in Appendix B, recommended that *After a long-standing debate on how to provide data to inform surveillance of periodontal disease, a recent multinational effort has suggested standard reporting of periodontal epidemiology surveys. Such efforts are important to provide comparable data across populations*.

Several international research efforts have actually made use of this definition for periodontitis cases. For instance, a recent study (51) that compared CDC/AAP Case Definition and the EFP/AAP Classification concluded that use of the EFP/AAP classification (as a possible new globally accepted classification) to assess periodontitis prevalence, severity and risk factors when conducting epidemiological surveys may not be totally reliable for use in population surveys. Hence the use of CDC/AAP in these studies is deemed more appropriate. Also, a recent systematic review and meta-analysis of the association of periodontitis with hypertension determined the CDC/AAP as a confident case definition of periodontitis (3).

The implementation of this classification improved reporting quality and permitted meaningful comparisons of the prevalence of periodontal diseases across populations in epidemiological studies (48). Indeed, many recent epidemiological studies with diverse populations in different parts of the world have used this classification (52–57), as well as (58–61) and (61–63).

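### The step that treats oral-health trajectories as risk factors for hypertension names only neural networks, which do not by default give an adjusted effect with a confidence interval and could easily overfit the few events available

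*Protocol article*

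**What the plan says.** Section 9.1.2 (Longitudinal Analysis) sets out the trajectory work in two steps. First, "Starting with the third evaluation (baseline evaluation + first follow-up + second follow-up), trajectories of oral health conditions will be identified", and the factors associated with each trajectory are to be found. Second, "trajectories will be considered as risk factors for the development of hypertension in the study participants and will be included in neural network models". No effect measure and no other model is attached to the second step.

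Section 3.6.2 fixes the spacing of the oral examinations: "The periodontal evaluation will be done every year". Section 3.6.1 has blood pressure assessed every two years.

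The only figures that bear on the number of events are in section 3.3.1:
- a design that "achieves 90% power with 0.05 significance";
- an exposure split of "90% of whom are in group X = 0 and 10% are in group X = 1";
- an "estimated value of incidence of hypertension of 21.5" per cent;
- "This change corresponds to a Relative Risk (RR) of 2.4";
- "A 40% dropout rate is expected", taking 866 to 1,212.

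**The concern.** The wording asks whether trajectories are risk factors. Answering that needs a measure of effect, held against confounders, with a statement of its uncertainty. The first hypothesis (section 2.3) shows the standard that the study sets for such a claim about periodontitis: risk over 60 months, controlled for sex, age, smoking, oral hygiene habits, education, occupation and marital status. A neural network in its ordinary use returns predicted risks, and none of these outputs comes with it unless further steps are specified.

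If the step runs as written, the trajectory analysis could end with a measure of predictive performance and no estimate that supports or refutes a statement that a given trajectory raises the risk of hypertension. With few events, apparent performance can also look better than it is unless the network is small, penalised or validated.

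**Working it through.** **1. Is another model named for this step?**
- Section 9.1.1 lists logistic, Poisson and other regressions with covariate control, under the cross-sectional heading.
- Section 9.1.2 lists generalized linear, logistic and multinomial models. There the oral variables are the outcomes, and factors such as smoking are the predictors.
- The association analysis later in 9.1.2 compares two groups, with and without periodontitis. It does not use trajectories.
- Section 9.2.4 names Cox, proportional hazards and logistic models beside neural networks, but for the microbiome.

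None of these assigns an adjusted model to trajectories as predictors of hypertension.

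**2. The plan's own sample size.** The standard formula for logistic regression on a binary covariate, with B = 0.10 exposed and overall risk P = (1−B)P0 + B·P1, is

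N = [z(1−α/2)·√(P(1−P)/B) + z(power)·√(P0(1−P0) + P1(1−P1)(1−B)/B)]² / [(P1−P0)²(1−B)], divided by (1−R²) for covariates.

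- 21.5% as the exposed risk, P0 = 0.215/2.4 = 0.0896, two-sided 0.05, 90% power, R² = 0: N = 864, against the stated 866. Applying the stated R² of 0.3 gives 864.4/0.7 = 1,235.
- 21.5% as the overall risk, 2.4 read as an odds ratio, one-sided, R² = 0.3: N = 867.
- 21.5% as the unexposed risk with RR 2.4, two-sided: 266 without the R² adjustment and 380 with it.

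Two different readings reproduce 866, so the figure does not settle which group the 21.5% describes. All three readings are carried forward. The third, which gives the most events, fits the stated size least well.

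**3. Events over 60 months.** Completers = 1,212 × (1 − 0.40) = 727. Events = 727 × overall risk.

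| 21.5% is the risk in | Overall risk | Events |
|---|---|---|
| the exposed (RR 2.4) | 0.1 × 0.215 + 0.9 × 0.0896 = 0.102 | 74 |
| everyone | 0.215 | 156 |
| the unexposed (RR 2.4) | 0.9 × 0.215 + 0.1 × 0.516 = 0.245 | 178 |

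**4. Events after the trajectory window.** With yearly examinations (baseline, month 12, month 24), the third evaluation falls at month 24. Under a constant event rate, the share that follows is 36/60 = 0.6.
- 74 × 0.6 ≈ 45
- 156 × 0.6 ≈ 94
- 178 × 0.6 ≈ 107

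If 866 rather than 727 are analysed, the ranges are 88 to 212 over 60 months and 53 to 127 after the window.

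**5. What network size would mean.** The article gives no layers, nodes, inputs or penalty, so these sizes are illustrations only. One hidden layer with p inputs and h nodes has h(p+1) + h + 1 weights.

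| Inputs, nodes | Weights | Events per weight at 45 to 107 events |
|---|---|---|
| 5, 1 | 8 | 5.6 to 13.4 |
| 10, 2 | 25 | 1.8 to 4.3 |
| 10, 5 | 61 | 0.7 to 1.8 |
| 20, 10 | 221 | 0.2 to 0.5 |

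A hazard model with trajectory class as 2 or 3 indicators plus the covariates of the first hypothesis needs about 10 to 15 parameters. That is 45/15 = 3 to 107/10 ≈ 11 events per parameter, so it too must be kept small or penalised.

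**The case against.** The best defence has four parts.

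- **The sentence need not exclude regression.** It says that trajectories will be considered risk factors and also that they will go into networks, and it opens by likening this to the preceding association step. That preceding step names no model either, however. Where the authors want classical models beside machine learning, as in section 9.2.4, they say so. The gap at this step stands.
- **A network can be made to yield an adjusted contrast.** With no hidden layer and a logistic output it is logistic regression. With confounders as inputs, predicted risks can be standardised over trajectory classes and bootstrapped. This is correct. A reader might infer that a network could never answer the question however it is tuned, and the documents do not support that. What stands is that the output is not supplied by default and that the article names no such step.
- **The architecture is unknown.** A reader might infer that the network has more parameters than the events can support. That cannot be derived: no architecture is given, a very small network would fit, and raw weight counts ignore penalisation. Leaving such detail to a fuller plan is normal for an article and is not criticised here.
- **Trajectories are secondary.** They appear in no objective, specific goal or hypothesis in section 2, and the periodontitis question has its own two-group analysis. A reader might infer that five years of examinations would yield only a black-box prediction. The incidence, relative-risk and two-group analyses in 9.1.2 show otherwise. The point is confined to the trajectory step.

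**Conclusion.** The point holds in a limited form. For trajectories as risk factors for hypertension, the article names a method that does not by default return an adjusted effect with a confidence interval, and no other section fills the gap. Overfitting is a real risk for any network that is not very small or penalised, but how large that risk is depends on an architecture that the article does not give.

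The event range rests on three assumptions: that the 21.5% may describe any of three groups, that 40% of 1,212 are lost and contribute no events, and, for the period after the window, that the event rate is constant and the third evaluation is at month 24. The range after the window is the one that matters here, since only later events can be attributed to a trajectory already formed. The periodontitis analysis itself is not affected.

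**What to change.** In section 9.1.2, state that the trajectory-hypertension estimate comes from a parsimonious hazard model, discrete-time or interval-censored because blood pressure is assessed every two years. It should cover hypertension arising after the trajectory window, among participants still free of it at that point. Enter trajectory class as a categorical term with the covariates of the first hypothesis, limited in number or penalised to suit the event count, and report hazard ratios with 95% confidence intervals. Describe neural networks as an exploratory prediction exercise, reported with cross-validated discrimination and calibration.

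The change is to analysis wording and uses data already planned. The cost is a little extra analysis, and the intervals will be wide because events are few.

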### 9.2. Microbiota Analysis

Bacterial DNA isolation and purification will be performed using the Qiagen Gentra Puregene Yeast/bacteria Kit, following the manufacturer's instructions to isolate DNA from Gram positive bacteria.

#### 9.2.1. Amplification of the 16S rRNA Gene

The purified DNA samples will be amplified with universal F24/Y36 primers to build wide coverage libraries. Additional libraries will be generated to expand the coverage of *Bacteroidetes* from the TM7/SR1 and *Spirochetes*/*Synergistetes* groups that will be amplified with primers of type F24/F01 or F24/M98. PCR cycles will be performed in thin-walled tubes in a Perkin Elmer 9700 (or higher) thermal cycler. The reaction mixture (50 μl final volume) will contain 1 μl of purified DNA template, 20 pmol of each primer, 40 nmol dNTPs, 2.5 units of Taq polymerase Platinum (Invitrogen, Carlsbad, CA) and 5 μl buffer 10X for PCR (200mM Tris-HCL, pH 8.4, 500 mM KCl). Following these steps, the warm-start protocol of tempered-elongation amplification will be followed and optimal amplicon sizes will be determined using agarose gels, following the standard procedure with the Qiagen gel extraction kit (Qiagen, Valencia, CA).

#### 9.2.2. Library Screening and 16S Sequencing

These procedures will be performed using 16S easy kits following the procedures for sequencing in Illumina technology (San Diego, CA).

#### 9.2.3. Design of the Computational Analysis of Microbiomes

The computational analysis of the microbiota data, and the strategy of curing, documentation and archiving of the metagenomic data will be carried out according to the *CAMI* guidelines (Critical Assessment of Metagenome Interpretation) that emphasizes the implementation of workflows that ensure reproducibility, following the Docker packaging approach in “Bioboxes” adapted for the analysis of the 16S rRNA region (100, 101).

#### 9.2.4. Design of the Association Studies of the Microbiome With Clinical, Social Variables, and Risk Factors

In order to determine the relationships between the oral subgingival microbiome with response variables (clinical, biochemical, socioenvironmental, lifestyle, among other risk factors) a hybrid design has been chosen that combines classic approaches to epidemiology and biomedical statistics (proportional hazards models, Cox regressions, multivariate and logistic, transformed variables, etc.) with contemporary analysis methodologies based on computational learning ideas (neural networks, deep learning, support vector machines, Bayes naive-type models, decision trees, etc.). The choice between models will consider principles of maximum likelihood and maximum parsimony.

## 10. Design and Implementation of the Data Management Plan

The purpose of the Data Management Plan is to establish guidelines on how the data will be treated during the course of the project and what will happen to this data at the end of the project. This document will detail what will be done with the data from its collection, its organization, pre-processing, analysis, quality controls, data preservation techniques, and documentation of the databases. Likewise, the conditions of use, dissemination, sharing options, embargoes and limitations are stipulated. To this end we will follow the general recommendations of the *Clinical Data Management Plan Committee* (102).

## 11. Design of the Communication Strategy and Socialization of the Results

Given that HBP is an important public health problem, that its pharmacological treatment is complex and expensive, and that its consequences (individually and collectively) are serious, we consider a patient-centered approach to primary and secondary prevention, as the strategy with the greatest potential to promote the results of this study. For this reason it is especially relevant in the Mexican context in which this project is immersed to have an agile strategy for communicating the results and scope of our work, as well as for the socialization of knowledge. We believe that this will allow to have a direct positive impact on the population, particularly in participants at risk who should be well informed about the association between HBP and periodontitis, to have access to timely counseling to identify risk factors, and to receive timely medical and dental attention (103, 104).

Additionally, our results may have an impact on public policy through recommendations for direct government actions and programs, whose implementation is, by their very nature, of much longer scope. Especially in view of the next months or years, while the COVID19 pandemic remains, and time after, we will have to implement novel strategies in public dental health and a multilevel approach for hypertension control (8, 105). For example, by using teledentistry and telemedicine, mobile health applications or the use of social networks as contact means to follow and communicate with patients (106–109).

## 12. Discussion

Cardiovascular diseases and arterial hypertension are complex patho-phenotypes responsible for a large burden of morbidity and mortality worldwide. Early diagnosis and interventions are key to better control these diseases. Hence, the current protocol study aims to understand the relationship between the onset of arterial hypertension, periodontitis and the role that periodontal microbiome, as well as social determinants and risk factors that may be playing in the interrelationship between these issues.

The present protocol has been designed as a sub-cohort analysis of the larger cohort investigating the factors behind the onset of hypertension (35). This sub-cohort analysis has been planned to include a close follow-up of participants for which studies on blood pressure, periodontal health, and the oral and subgingival microbiome, will be supplemented with information on participants' lifestyle and nutritional habits, social determinants of health and risk factors.

These studies will be carried out by a multidisciplinary, multi-centric team that incorporates researchers from university settings (represented by the Graduate Division of the School of Dentistry at the National Autonomous University of Mexico), federal government institutions represented by three of Mexico's National Institutes of Health (National Institute of Cardiology Ignacio Chávez, National Institute of Geriatrics and National Institute of Genomic Medicine), and the support of researchers from the National Council on Science and Technology. As stated, the team will apply the best practices in dental public health and epidemiology, supported by rigorous sampling and laboratory protocols, state of the art statistical and computational analytic methods and a carefully designed and executed data management and data policy plan. All procedures will be performed following strict safety considerations; both in the management and sampling of participants, and in the processing of biological samples (even more stringent in the face of the recent COVID-19 pandemic).

This project has been planned with strong ethical foundations and respect to the participants' confidential or sensitive information. In view of the importance of translating basic findings into actionable interventions, this protocol will consider the implications of our findings, both in the generation of public policy, and for population empowerment, via the establishment of primary prevention—highlighting the relationship between oral and cardiovascular health. This latter set of interventions will be supported by a carefully planned science communication and health promotion strategy. All of the previously discussed goals are in line with our general view to contribute to the development of early interventions aimed at diminishing the devastating consequences of cardiovascular diseases, in particular by highlighting the relationship between periodontitis and arterial hypertension and the mediation of the oral subgingival microbiome.

